# Wearable Neurotechnology for the Treatment of Insomnia: The Study Protocol of a Prospective, Placebo-Controlled, Double-Blind, Crossover Clinical Trial of a Transcranial Electrical Stimulation Device

**DOI:** 10.3390/clockssleep7010003

**Published:** 2025-01-26

**Keywords:** transcranial electrical stimulation, insomnia, sleep onset latency, actigraphy, electroencephalogram

## Abstract

Sleep disruption and deprivation are epidemic problems in the United States, even among those without a clinically diagnosed sleep disorder. Military service members demonstrate an increased risk of insomnia, which doubles after deployment. This study will investigate the ability of a translational device, Teledyne PeakSleep™ (Teledyne Scientific & Imaging, Durham, NC, USA), to reduce sleep onset latency and the time spent awake after sleep onset, with improvement in the subjective benefits of sleep for patients with insomnia by enhancing the brain rhythms within the frontal lobe implicated in slow wave generation. During this crossover trial, patients will use the wearable neurotechnology prototype headband, which delivers < 14 min of frontal short duration repetitive–transcranial electrical stimulation over a 30 min period immediately before trying to fall asleep. Using active stimulation versus a sham paradigm, we will compare actigraphy data, physiological data, and subjective sleep measures against a pre-treatment baseline in the same patient over the course of the 8-week study. If successful, PeakSleep™ could address the final common pathway in insomnia, namely the onset and maintenance of slow-wave sleep (SWS), and accordingly has the potential to enhance sleep onset in a wide range of individuals, most importantly warfighters in whom efficient sleep onset may be critical for operational success.

## 1. Introduction

Insufficient sleep syndrome, often with comorbid insomnia, has become a health problem of epidemic proportions within the United States military. Over 50% of warfighters chronically sleep less than 6 h per night while on deployment or in their garrison. Consequently, they are predisposed to workplace injury, cognitive and physical health compromises, poor morale, a weakened immune system, and fatal/costly accidents [1,2,3,4]. One-half to two-thirds of the 2.5 million U.S. military troops that have served in Afghanistan and Iraq have reported insomnia after returning home [5,6,7]. Issues with insomnia persist in veterans and frequently worsen with age, creating a huge burden on the Veterans Affairs (VA) healthcare system [8].

In addition to our veteran and active-duty population, sleep disruption and deprivation remain an epidemic problem in the United States, even among those without a clinically diagnosed sleep disorder [9,10]. There are a large number of available pharmacological sleep aids and cognitive behavioral therapies for healthy individuals, but each comes with recurring costs, limited access, short-term efficacy, and potentially undesirable side effects [2,11,12]. By comparison, transcranial electrical stimulation (tES) has been demonstrated to be safe across thousands of users and carries a favorable side effect profile, with the primary side effect of low-dose tES being a tingling, prickly, or itchy sensation at the electrode site [13,14]. tES has been shown to enhance deep sleep and memory consolidation when applied during a nap or overnight sleep [15,16,17,18,19]. Recently, several studies and ongoing trials have investigated whether tES applied prior to sleep or during nighttime awakenings can achieve similar benefits to tES during sleep by reducing sleep onset latency (SOL), increasing sleepiness, or improving subjective sleep quality [20,21,22,23,24,25].

Recognizing the clinical and operational needs for improving sleep onset and quality, Teledyne developed a field-ready, wearable neurotechnology device for sleep modulation called PeakSleep™. The device consists of a soft fabric headband with integrated electronics for dry electroencephalogram (EEG) sensing and electrical stimulation (see Figure 1). Teledyne internally investigated tES with a phase I study in 2019–2020 in 23 civilian participants with sleep onset insomnia who were randomized in a double-blinded, sham-controlled crossover study. The trial replicated previously reported work demonstrating that applying tES (0.75 Hz) over the forehead prior to sleep onset can enhance inter-stimulus delta power. Teledyne’s study revealed a reduction in SOL with a remarkably large effect size for a trial with only 23 participants (Cohen’s d = 1.3) (manuscript in preparation). Furthermore, patients reported an overall sleep benefit and improved sleep quality on a Likert scale. These results provided the first-in-human clinical evidence of a safe, robust, and portable sleep priming device.

Building on this trial, Teledyne Scientific & Imaging, Limited Liability Company, (LLC) and the Uniformed Services University of the Health Sciences (USU) have partnered together to further investigate the device’s ability to reduce SOL and wakefulness after sleep onset (WASO) while improving restfulness and subjective sleep for patients with insomnia. We hypothesize that by applying tES across the forehead/mastoid, we can impose slow oscillations within the cortex during wakefulness prior to sleep, and the brain will be more likely to enter a sleep state. We aim to develop and demonstrate a new treatment option for patients with insomnia that is effective, safe, and poses a favorable side effect profile.

## 2. Experimental Design

### 2.1. Study Design

The tES study (Wearable Neurotechnology for the Treatment of Insomnia) is a prospective, placebo-controlled, double-blind, crossover phase II clinical trial of a non-significant risk device used to treat individuals with sleep-onset insomnia. This study will be run as a single investigational site study with Teledyne Scientific & Imaging, LLC (Durham, NC, USA), as the Sponsor, and the Uniformed Services University of the Health Sciences (USU) as the trial investigation site. The study will involve five in-person visits to the study site, each separated by two weeks, for eight weeks total. Participants will be randomly assigned to either the short-duration repetitive–transcranial electrical stimulation (SDR-tES) intervention treatment or sham treatment condition on Visit 2 before crossing them over to the remaining condition on Visit 4. Each participant will receive a total of 14 days of exposure. Assignments will be counterbalanced among participants. Participants will not be followed up after the conclusion of the eight-week study.

### 2.2. Primary Outcome

We intend to measure the reduction in SOL between sham and stimulation groups using FitBit actigraphy data collected during baseline, treatment, and washout periods.

### 2.3. Secondary Outcomes

We intend to collect subjective survey data for insomnia (ISI) and psychiatric conditions [PHQ-9, PCL-5, STAI], sleep habits [daily sleep diary], HIT, and device experience during experimental sessions. Additionally, we will collect physiological data using actigraphy collected by FitBit Inspire 3 (FitBit Inc., San Franisco, CA, USA) to profile participants’ sleep measures, including their total sleep time (TST) and time spent awake after sleep onset (WASO) and EEG via PeakSleep™ (Teledyne Scientific & Imaging, Durham, NC, USA) to monitor the impact of the stimulation on brain function and activity.

### 2.4. Safety Outcomes

Adverse events (AEs) for this study fall into two different categories. Of note, we believe that the likelihood of these events remains very low.

a.Physical AEs: The final question in our daily sleep diary asks if the participant had any physical or cognitive effects when using the device. If they answer yes, they will be asked to contact study staff and immediately trigger the recording of an AE. Any physical AE will be assessed by study investigators as to their severity, and appropriate medical attention will be provided. Participants with less severe effects will be advised to discontinue the use of the device and treat it at home if possible. For patients with any severe interaction or more serious adverse effects, we will immediately refer them to medical help, and appropriate follow-up will be performed per our stopping criteria.b.Clinical/psychiatric AEs: There may also be a possibility of clinical or psychiatric adverse effects from the device, which will be assessed using the sleep diary, STAI for anxiety, and PHQ-9 for suicidal ideation. Patients are advised to note and report any changes in mood or cognition that occur during the trial.

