## 5. Detailed Procedure

### 5.1. Visit 1 (Enrollment)

If the participant meets all inclusion criteria, informed consent will take place prior to any experimental procedures. Once consent is given and participants understand the full scope of the study procedures, they will be asked to complete a demographics questionnaire, the patient health questionnaire (PHQ-9), the Posttraumatic Stress Disorder (PTSD) Checklist for DSM-5 (PCL-5), the State Trait Anxiety Inventory (STAI) and the Headache Impact Test (HIT). Suicidal ideation is one of the exclusion criteria for further participation indicated by item 9 on the PHQ-9. Any participant responding to this item with a score > 0 will be interviewed by the PI, and if further medical attention is deemed necessary, the participant will be dismissed from any further participation and referred to the appropriate medical help. If a participant fails to meet the inclusion/exclusion criteria for the study, then all data from screening materials (PHQ-9, PCL-5, STAI, HIT, ISI) will be deleted. Participants will be offered compensation of up to USD 1000 for the completion of the study, with an opportunity to receive compensation at the completion of each in-person visit. A detailed schedule of assessments to be collected during the 8-week study can be found in Table 2.

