### 5.3. Visit 3 (Washout)

During Visit 3, we will collect PeakSleep™ devices and administer a second ISI to assess participants’ response to treatment condition 1. Participants will also be requested to fill out a short questionnaire asking about the occurrence and details of any adverse events during the past two weeks with the device, which the investigator will review during the visit. Participants will complete another PHQ-9 to reassess any impact on depression or suicidal ideations. Participants will return home without the PeakSleep™ device but will continue to wear the actigraphy devices and complete the daily sleep diary in order to monitor sleep habits during a 2-week washout period. The purpose of the washout interval is to investigate any lingering effects from the first intervention and to ensure that those receiving the stimulation first return to a proper baseline prior to the sham treatment. Visit 3 will take approximately 1 h.

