### 5.5. Visit 5 (Study Exit)

Participants will return the actigraphy and PeakSleep™ devices. We will administer a final measurement of the ISI to assess the impact of the second treatment condition over the previous 2 weeks. Participants will again fill out the PHQ-9 to reassess any impact on depression or suicidal ideations. Participants will repeat the adverse event questionnaire and be asked to complete a questionnaire on their user experience with the device. Visit 5 will take approximately 1 h.

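### The diary question that triggers an AE record, as described, names neither mood nor anxiety, although section 2.4 relies on the diary to detect psychiatric effects

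*Protocol article*

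**What the plan says.** Section 2.4 of the protocol article divides adverse events into physical (a) and clinical or psychiatric (b).

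- Under (a): "The final question in our daily sleep diary asks if the participant had any physical or cognitive effects when using the device". The consequence follows: "If they answer yes, they will be asked to contact study staff and immediately trigger the recording of an AE".
- Under (b), psychiatric effects are those "which will be assessed using the sleep diary, STAI for anxiety, and PHQ-9 for suicidal ideation". The paragraph ends with a standing instruction: "Patients are advised to note and report any changes in mood or cognition that occur during the trial".

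The visit procedures add further routes. At Visit 3 (section 5.3) participants fill in "a short questionnaire asking about the occurrence and details of any adverse events during the past two weeks with the device", which the investigator reviews. In the same section, "Participants will complete another PHQ-9 to reassess any impact on depression or suicidal ideations". At Visit 5 (section 5.5), "Participants will repeat the adverse event questionnaire", and the PHQ-9 is given again. Section 5.1 and Table 2 place the STAI at Visit 1 only.

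**The concern.** The diary is the one instrument in 2.4(b) that is completed every day while participants use a brain-stimulation device at home without supervision. Yet the only diary AE item the article describes is worded for physical and cognitive effects and tied to device use. Mood and anxiety, which 2.4(b) is largely about, are not in it.

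What is at stake is the timeliness and consistency of safety capture. A participant whose mood or anxiety worsens between visits could answer the item as described with a truthful no. The event would then reach the study team only if the participant volunteered it, or at the end-of-period visit.

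**Working it through.** The plan gives no figure to reproduce. The check sets each instrument's described content against its timing (sections 2.4, 5.1, 5.3 and 5.5, and Table 2).

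| Route | Scope as described | When | Daily prompt for mood or anxiety in home use? |
|---|---|---|---|
| Diary, final question | physical or cognitive, during use | daily | neither is named |
| STAI | anxiety | Visit 1 only | no; precedes all stimulation |
| PHQ-9 | depression, suicidal ideation | Visits 1, 3, 5 | no; end of period |
| AE questionnaire | any adverse event | Visits 3, 5 | no; end of period |
| Standing instruction | mood or cognition | throughout | no; relies on the participant volunteering |

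**Content.** Section 2.4(b) and its closing instruction concern mood, anxiety and suicidal ideation. The described diary item names none of these three.

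**Anxiety.** Of the three instruments named in 2.4(b), the STAI cannot show anxiety arising on treatment, because it is given once, before the device is issued at Visit 2. The PHQ-9 is named there for suicidal ideation. That leaves only the diary to pick up anxiety after baseline, and its described AE item does not mention it.

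**Timing.** Stimulation is given immediately before the participant tries to sleep (Abstract). An effect noticed overnight or the next day is outside the literal wording of an item tied to device use.

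**Longest wait for a prompted assessment.** Visits are two weeks apart (section 2.1). For an effect starting after the first home session of a treatment period, the next described prompt that would cover it is the end-of-period visit, so the wait is up to 2 weeks × 7 days = 14 days. This assumes that the diary has no other mood or anxiety item and that the participant does not report spontaneously.

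**Washout.** The devices are collected at Visit 3, so an item tied to device use has nothing to refer to in the following two weeks. Table 2 marks neither the PHQ-9 nor the AE questionnaire at Visit 4. Section 5.3 nonetheless gives the study of lingering effects as one purpose of the washout.

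**The case against.** The strongest reply is that the diary itself is not shown. The article describes one item, calls it the final question, and places it under physical AEs. Section 2.4(b) does not say that this item is what detects psychiatric effects, and an earlier diary item may do so. An article commonly leaves the full diary to the full protocol. This stands as a limit: the point can be made only about the item as described. It does not remove the point, because the article chose to state the item and its trigger, and what it states does not match the use 2.4(b) makes of the diary.

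The second reply is that psychiatric effects have other stated routes: the standing instruction, which is not confined to sessions, and the PHQ-9 and AE questionnaire at Visits 3 and 5. There is also a supervised 5-minute trial session at Visit 2. This stands too. Such events are not left uncaptured; what is missing is a described prompt between visits.

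A reader might infer three stronger things that the documents do not support:

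- **That mood and anxiety effects cannot trigger a daily AE record.** Only one diary item is described, and its wording may be a paraphrase.
- **That the item covers only about 2% of the day** (30 min / 1440 min = 2.1%). This treats the article's description as the literal diary text limited to the session. Section 5.3 uses a similar phrase about the device for a whole two-week period.
- **That psychiatric AE counts are biased downward.** Nothing says that a diary no records the participant as event-free, or that counts come from the diary alone. The end-of-period questionnaires ask back over each treatment period. Any under-capture could affect both conditions, and no effect on their comparison is shown.

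**Conclusion.** The mismatch is real but small. Section 2.4(b) relies on the diary for psychiatric effects, while the only diary AE item and trigger described does not name mood or anxiety and is tied to device use. The STAI, named in the same sentence for anxiety, is scheduled only before stimulation. That second inconsistency can be verified in the article and does not depend on what the unseen diary contains.

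The consequence is possible delay, up to 14 days in a treatment period, and reliance on volunteered reports between visits. This rests on the diary having no further mood or anxiety item. A bias in final AE counts is not shown. Severity is low.

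**What to change.** If the full diary already has a mood or anxiety item that leads to an AE record, one sentence in section 2.4 saying so is enough.

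Otherwise, reword the final diary question in section 2.4 and in the app along these lines: *Since your last entry, have you had any new or worse physical, cognitive, mood or anxiety effects?* A yes would prompt contact with staff and an AE record, as now. Ask it in the same words in both conditions. The since-last-entry wording also covers effects noticed overnight or the next day, and it remains answerable in the washout.

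Separately, reconcile section 2.4's use of the STAI for device-related anxiety with its Visit 1-only schedule in section 5.1 and Table 2.

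The cost is one reworded question, notification of the ethics board, and somewhat more AE reports to review, mostly minor. Section 2.4(a) attaches handling advice to less severe physical effects, and section 3.2 makes inclusion depend on viable data from at least 8 of 14 sessions. The sponsor should therefore state how mood and anxiety reports would be handled. That is a clinical decision left to the sponsor, and the rewording itself changes no dose, schedule or stopping rule.

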### 2.5. Eligibility Criteria

Participants are eligible if they are at least 18 to 70 years old, have been diagnosed with sleep-onset insomnia or a self-reported insomnia diagnosis (Insomnia Severity Index score ≥ 15), have sleep onset latency > 30 min 6 months prior to enrollment, and no pharmacologic or non-pharmacologic treatment for insomnia in the last 14 days, including sedating medications at bedtime. Patients who meet any of the exclusion criteria (see Table 1) on the day of consent will be excluded.

After potential participants are selected, the study team will obtain informed consent approved by the USU Institutional Review Board (IRB). Participants will be free to withdraw consent and discontinue participation at any time without prejudice. In addition, the PI may end a participant’s participation in this study for any of the following reasons: (1) if the participant develops any condition that in the judgment of the PI may place them at risks not described above or at greater severity for those described above by continuing his/her participation; (2) if the participant becomes pregnant; (3) if the participant is unable to keep his/her scheduled sessions; (4) if the study is halted by the sponsor, the IRB, or the FDA; and (5) for administrative reasons.

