### 5.2. Visit 2 (Treatment 1)

Participants are block-randomized to treatment conditions based on the order (sham or stimulation first) and will be balanced with respect to gender. Participants who successfully complete 2 weeks of baseline collection will be enrolled in the first treatment group of their assigned order. To assess their insomnia baseline, they will complete the Insomnia Severity Index (ISI) during this visit. They will be trained on the use of the PeakSleep™ device and sent home for 2 weeks. The PeakSleep™ device will deliver therapy and collect EEG data for the investigation of neural activity for both stimulation and sham conditions. The participant’s response to the first treatment condition will also be measured with actigraphy and a daily sleep diary completed on a phone app, which also controls the PeakSleep™ device.

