^1^ Safety data for tES use in pregnant women are scarce, and we will exclude this population if the questionnaire reveals they are pregnant or are trying to become pregnant. In the event that the patient is untruthful regarding their pregnancy status, we view the risk as insignificant given the reported studies and the fact that our dose is less than one-fourth of the dose used in such studies.

**Table 2 clockssleep-07-00003-t002:** Detailed schedule of assessments during 8-week data collection period.

	Timepoint				
Assessment	Visit 1	Visit 2	Visit 3	Visit 4	Visit 5
Informed Consent	X				
Patient Health Questionnaire	X		X		X
Posttraumatic Stress Disorder Checklist for DSM-5	X				
State Trait Anxiety Inventory	X				
Headache Impact Test	X				
Insomnia Severity Index		X	X	X	X
Daily Sleep Diary	X	X	X	X	X
Adverse Events Questionnaire			X		X
Device Experience Questionnaire					X
FitBit Actigraphy Data		X	X	X	X
PeakSleep™ EEG Data			X		X

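### The STAI is named to assess device-related anxiety but is scheduled only at Visit 1, before any device use; PCL-5 and HIT, listed as secondary outcomes, are also measured only then

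*Protocol article*

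**What the plan says.** Section 2.4 (Safety Outcomes) allows for clinical or psychiatric adverse effects of the device, "which will be assessed using the sleep diary, STAI for anxiety, and PHQ-9 for suicidal ideation". Section 2.3 (Secondary Outcomes) says the trial will collect "subjective survey data for insomnia (ISI) and psychiatric conditions [PHQ-9, PCL-5, STAI], sleep habits [daily sleep diary], HIT, and device experience during experimental sessions".

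The timing is given in two other places. Section 5.1 (Visit 1) lists the questionnaires completed after consent: demographics, PHQ-9, PCL-5, "the State Trait Anxiety Inventory (STAI) and the Headache Impact Test (HIT"). Table 2, titled "Detailed schedule of assessments during 8-week data collection period", has a row for the "State Trait Anxiety Inventory" with one mark, under Visit 1. The PCL-5 and HIT rows are the same.

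For the ISI, section 2.5 gives as one entry route a "self-reported insomnia diagnosis (Insomnia Severity Index score ≥ 15"). Section 5.1 counts the ISI among the screening materials. Section 5.2 places its first administration at Visit 2: "To assess their insomnia baseline, they will complete the Insomnia Severity Index (ISI) during this visit". Table 2 agrees, with marks at Visits 2 to 5.

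**The concern.** Assessing an adverse effect of a device with a rating scale requires at least one score taken after the device has been used. Judging whether an effect belongs to the stimulation rather than to the sham requires a score from each treatment period. If the STAI is given only before exposure, the plan names an anxiety instrument that cannot show anxiety caused by the device.

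The same reasoning applies, with less at stake, to PCL-5 and HIT. An outcome listed for collection in the experimental sessions is expected to be reportable by condition, and a single pre-exposure value is not.

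The loss could not be made good later, because section 2.1 provides for no follow-up after the eight weeks. The ISI raises a smaller question: a threshold used at entry should have a stated time of measurement before entry.

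**Working it through.** There is no stated figure to reproduce. The check sets the schedule against the roles given to each instrument.

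**Timeline.** Section 2.1 gives five visits two weeks apart, so Visits 1 to 5 fall at weeks 0, 2, 4, 6 and 8. The device is first used at Visit 2 (training session, section 5.2). Visit 3 ends the first treatment period, Visit 4 ends the washout and Visit 5 ends the second treatment period.

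**Administrations (Table 2, checked against sections 5.1 to 5.5).**

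| Instrument | Scheduled at visits | Count at Visits 3 to 5 (after first exposure) |
|---|---|---|
| STAI | 1 | 0 |
| HIT | 1 | 0 |
| PCL-5 | 1 | 0 |
| PHQ-9 | 1, 3, 5 | 2 |
| ISI | 2, 3, 4, 5 | 3 |
| Adverse event questionnaire | 3, 5 | 2 |

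The visit narratives agree with the table. Visit 3 has the ISI, the adverse event questionnaire and the PHQ-9. Visit 5 has the same three plus the device experience questionnaire. Neither mentions STAI, HIT or PCL-5, so a table broken in conversion does not explain the result.

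**What a single Visit 1 score supports.** Write Y1, Y3 and Y5 for scores at Visits 1, 3 and 5. Change over the first period is Y3 − Y1. For a participant who has active treatment first, the active-minus-sham contrast is (Y3 − Y1) − (Y5 − Y1) = Y3 − Y5. Both need Y3, and the second also needs Y5. With only Y1 neither can be calculated, and the score can serve only as a baseline descriptor or covariate.

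**Size.** The recruitment target is 48 completers (section 2.7). End-of-period STAI scores as scheduled: 48 × 0 = 0. With Visits 3 and 5 added: 48 × 2 = 96.

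**Agreement with the analysis section.** Section 3.2 names only ISI and PHQ-9 as the subjective measures to be modelled over time. This fits Table 2, so it is sections 2.3 and 2.4 that disagree with the rest of the article.

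**ISI.** Section 5.1 names five screening instruments: PHQ-9, PCL-5, STAI, HIT and ISI. The Visit 1 list in the same section and the Visit 1 column of Table 2 contain the first four and omit the ISI. The first scheduled ISI is at week 2, as the insomnia baseline.

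**The case against.** **Other safety capture remains.** This is true and limits the consequence. After exposure there are the daily diary with its adverse-effect question, the instruction to report changes in mood or cognition, the adverse event questionnaire at Visits 3 and 5 (reviewed by the investigator at Visit 3), and the PHQ-9 at both visits. A reader might infer that psychiatric safety is not monitored at all; the article does not support that. What is missing is the standardised anxiety score. Section 2.4 assigns the PHQ-9 to suicidal ideation, and its diary item concerns bodily or cognitive effects, so neither replaces the STAI in the role given to it.

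**PCL-5 and HIT were never promised an analysis.** This largely stands. Section 2.3 speaks only of collecting them, section 3.2 does not model them, and section 2.4 gives them no safety role. It would be tempting to say that device-related headache can no longer be detected by the instrument meant for it, but no section names HIT for that purpose. The remaining fault is that they are listed as secondary outcomes from the experimental sessions when the schedule makes them baseline measures.

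**The ISI entry check may happen at screening.** A reader might infer that the entry threshold cannot be applied, or that people below it will be enrolled and found only at randomisation. The documents do not support this. Section 5.1 counts the ISI as screening material, section 2.7 mentions a screening appointment, and Table 2 covers only the eight-week data collection period. As worded, the threshold is attached to the self-report route, with a diagnosis of sleep-onset insomnia as the alternative, so the ISI does not clearly decide entry for everyone. Against this, Table 2 shows the other four screening instruments at Visit 1, so its scope does not explain why the ISI alone is absent. What is left is a timing inconsistency.

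**A journal article condenses the full protocol.** That would excuse an omission. Here the article positively places the STAI at Visit 1 only, in both text and table, while giving it a safety role that needs later scores. An analysis plan cannot supply data that were not collected.

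**Conclusion.** The point holds for the STAI: section 2.4 contradicts section 5.1 and Table 2. Followed as written, the schedule gives 0 post-exposure STAI scores per participant, so the named instrument can show neither device-related anxiety nor a difference between active and sham. For PCL-5 and HIT the fault is one of labelling: each is called a secondary outcome but measured only before exposure, so it can only describe the sample. For the ISI there is only an unclear time for the entry measurement.

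The conclusion assumes that Table 2 and the visit narratives, which agree, are the schedule in force. If the full protocol gives the STAI at later visits, the correction is to the article's table and text. The primary SOL outcome, the sample size and the main treatment comparison are not affected.

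**What to change.** 1. Add the STAI at Visits 3 and 5, beside the PHQ-9, in Table 2 and sections 5.3 and 5.5, and compare change from Visit 1 between active and sham.
2. For HIT and PCL-5, either add them at Visits 3 and 5 or relabel them in section 2.3 as baseline measures.
3. State in section 5.1 and Table 2 when the entry ISI is taken, and keep the Visit 2 ISI as the analysis baseline.

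The cost is a small amendment and a few minutes of self-report at Visits 3 and 5, each already planned for about 1 h. Relabelling and stating the ISI timing are edits to the text and table. No extra visit is needed.
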